### Adherence and treatment integrity

All therapists are supervised bi-weekly by an experienced clinical psychologist (HK, TK) to ensure treatment integrity. In this supervision, all cases are discussed. Therapists register each face-to-face, video, phone and e-mail contact with the participant. The duration of the contact and treatment modules delivered are registered. All activities of the participant and therapist on the platform are registered via log data and are available for analysis.

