### Care as usual

After randomisation, participants in the care as usual condition have no access to *Fit after COVID* during the study, but are not restrained from using any form of care for fatigue or other COVID-19 related symptoms. Care as usual for post-COVID-19 patients can entail follow-up contacts with their treating physician or GP, physical training, occupational therapy or rehabilitation. At T1, all participants are questioned about the care they received since baseline assessment. Participants who are still severely fatigued, i.e. a score of ≥ 35 on the CIS-fatigue at T2, and voice a care need can be referred for CBT for severe fatigue; this will be provided by the ECCF of the Amsterdam UMC.

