### Randomisation

Allocation of participants to either CBT or care as usual is stratified based on (1) illness severity during the acute stage of COVID-19 (no admission to hospital; admitted to hospital, not on the intensive care unit (ICU); ICU during hospitalisation) and (2) dyspnoea based on the Medical Research Council (MRC) [59] score (< 3 vs. ≥ 3). This is because dyspnoea might influence the response to CBT by interfering with the graded activity module. A web-based randomisation programme in Castor EDC [60] is used to generate the randomisation sequence. The allocation ratio is 1:1. Block-randomisation with randomly selected block sizes (i.e. 2, 4 or 6) is used. The randomisation is performed by a research assistant in the presence of the participant who is on the phone. The research assistant, the researcher and the participants are blinded to the allocation sequence. Due to the nature of the intervention, blinding to allocation is not feasible. Data will be analysed by an independent statistician using a data file which is blinded for treatment allocation.

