### Statistical analyses

Descriptive statistics (i.e. participant characteristics) will be presented in tables, with separate columns for participants randomised to CBT vs. participants randomised to care as usual. Categorical variables (e.g. sex, relationship status) will be presented in participant numbers (*n*) and percentages (%). Continuous variables (e.g. age, CIS-fatigue baseline score) will be presented in means and standard deviations (SD) or, if appropriate due to skewness of data, as median with its interquartile range. Participant numbers, dropout and reasons for dropout will be presented in the study flow-chart. In all analyses, two-sided *p* values of < 0.05 are considered to indicate statistical significance. All analyses will be conducted in SPSS.

Change in fatigue scores between T0 and T1 for each individual participant will be shown in a figure using the Leeds RCI calculator [86]. This figure will show whether the change was clinically significant and reliable, or reliable only, and if there was no change or a deterioration in fatigue.

The primary study parameter will be analysed according to intention-to-treat, i.e. all randomised participants will be included in the analysis and they are analysed in the group to which they were randomly allocated. The primary hypothesis will be tested using a mixed linear model. The model will include T1 and T2 fatigue severity score as a dependent variable, condition (CBT vs. care as usual), time (T1, T2), condition by time interaction as fixed effects, a random intercept and the fatigue severity score at baseline as covariate. It will be examined if the main effect of condition from the mixed linear model, i.e. the mean difference in CIS-fatigue scores across T1 and T2 while controlling for baseline fatigue, is statistically significant. If the main effect of condition is found to be statistically significant, the statistical significance of the between group differences at the separate time points (T1 and T2) will be interpreted.

Cohen’s d effect sizes will be calculated by dividing the parameter estimate for the mean difference in CIS-fatigue scores between both conditions from the mixed linear model by the pooled standard deviation of both conditions combined. Effect size magnitudes will be interpreted as small (0.2 to 0.5), medium (0.5 to 0.8) and large (greater than 0.8) [87].

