To explore the robustness of our findings from the primary analysis, four sensitivity analyses will be conducted. First, per protocol analysis will be conducted. Treatment completion will be operationalized in two ways, i.e. by including (a) participants who have filled out the treatment goals and opened the standard modules of the intervention and (b) participants who have completed the intervention according their therapist.

Second, as the primary outcome consists of the mean CIS-fatigue score across T1 and T2, the extent to which our result would change if based on a single time point will be explored. Therefore, the analysis with the CIS-fatigue score at T1 as a dependent variable and with the CIS-fatigue score at T2 as a dependent variable adjusted for CIS-fatigue score at baseline using analysis of covariance will be repeated. For each of the time points Cohen’s d effect sizes will be calculated.

Third, the extent to which dyspnoea at T0, disease severity, time since diagnosis of COVID-19, age and sex have an impact on the primary outcome will be explored, and whether this impact differs between CBT and care as usual. These analyses will be conducted by including these variables and their interaction-terms with condition as covariates in the mixed linear models.

Fourth, missing values will be replaced with multiple imputation using chained equations and the data will be reanalysed. The imputation model will include all baseline sociodemographic and clinical characteristics assessed at baseline and follow-up measurements. A total of five data sets will be imputed and pooled according to Rubin’s rule.

Secondary outcomes will also be analysed according to intention-to-treat. For T1 and T2, it will be determined if there is a clinical meaningful improvement in fatigue, defined as a RCI [84] of more than 1.96 and a decrease of the fatigue level to a normal range (i.e. a score of < 35 on the CIS-fatigue). For secondary outcomes that are dichotomous, separate logistic regression analysis will be done for T1 and T2. For secondary outcomes that are continuous (i.e. physical functioning, work and social adjustment, somatic symptoms, cognitive symptoms), differences between CBT and care as usual will be analysed using mixed linear models as described above.

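### The per-protocol sensitivity analysis selects participants on completion in the CBT arm only, so it is open to selection bias and cannot by itself show that the intention-to-treat result is robust

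*Protocol article*

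**What the plan says.** All references are to the protocol article.

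- **Role of the analysis.** Statistical analyses introduces it with: "To explore the robustness of our findings from the primary analysis, four sensitivity analyses will be conducted. First, per protocol analysis will be conducted".
- **Definition (a).** It includes "participants who have filled out the treatment goals and opened the standard modules of the intervention".
- **Definition (b).** It includes "participants who have completed the intervention according their therapist". No criterion for the therapist's judgement is given.
- **Care as usual.** No per-protocol criterion is stated for this arm. Under Care as usual, these participants cannot use the intervention while in the study, but they "are not restrained from using any form of care for fatigue or other COVID-19 related symptoms".
- **Primary analysis.** It is by intention to treat: "all randomised participants will be included in the analysis and they are analysed in the group to which they were randomly allocated". Besides condition, time and their interaction, the mixed model has "a random intercept and the fatigue severity score at baseline as covariate". No adjustment for predictors of completion is mentioned.
- **Blinding.** Randomisation states: "Due to the nature of the intervention, blinding to allocation is not feasible".
- **Records available.** Adherence and treatment integrity states: "All activities of the participant and therapist on the platform are registered via log data and are available for analysis". Therapists also register their contacts and the modules delivered.

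**The concern.** Completion happens after randomisation and can be observed only in the CBT arm. Keeping completers there, while care as usual stays whole, compares a selected group with an unselected one. People who stay with a 17-week therapy may have a different outlook from those who stop, even without the therapy. Baseline fatigue is the only covariate named, and it need not capture that difference.

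Definition (b) adds a second route. The treating therapist knows the allocation and follows the patient's progress. According to Table 2, the treatment goals are activities to be taken up once fatigue eases, and the closing module works on those goals and reviews progress. A judgement that therapy is complete could therefore partly follow improvement in fatigue, which is the primary outcome. Definition (a) rests on recorded actions and is less exposed to this, but it is just as one-sided.

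At stake is interpretation. A per-protocol effect as large as or larger than the intention-to-treat effect could be presented as support for robustness, although selection alone can produce a difference.

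**Working it through.** **1. The plan's own figure.** The article gives no figure for the per-protocol analysis. Its sample size supplies the scale.

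- Inputs (Sample size calculation): SD 12, T1–T2 correlation 0.4, difference 6, two-sided 0.05, 80% power, 20% dropout.
- SD of the two-visit mean = 12 × √((1 + 0.4)/2) = 10.04.
- The normal approximation gives n = 44 per arm (stated 45). Power at 45 per arm is 80.9% (stated 80%).
- 45/0.8 = 56.25, rounded up to 57 per arm, 114 in total. The stated figures reproduce.

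**2. Size of the selection bias when the true effect is zero.** Let c be the completion share in the CBT arm. Let D be the difference in untreated CIS-fatigue between would-be non-completers and would-be completers that remains after baseline adjustment. Randomisation gives the whole CBT arm the same untreated mean as care as usual. Restricting to completers shifts it by

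bias = (1 − c) × D, positive when it favours CBT.

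Neither c nor D is in the article. Assumed ranges: c = 70–90%, D = 4–8 points.

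| c | D | Bias (points) | Share of 6 points |
|---|---|---|---|
| 0.9 | 4 | 0.4 | 7% |
| 0.8 | 4 | 0.8 | 13% |
| 0.8 | 8 | 1.6 | 27% |
| 0.7 | 8 | 2.4 | 40% |

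If D = 0 the bias is zero. If D is negative, for example because early recoverers stop, it runs against CBT.

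**3. Cross-check with a second model.** Suppose the propensity to complete is normal and correlates r with better outcome, and completers are the upper fraction c. Then bias = r × φ(z)/c × 10.04, where φ is the standard normal density and z is the (1 − c) quantile. The rejection rate is for a two-sided 5% test of 57c completers against 57 care-as-usual participants, with a true effect of zero and no missing outcomes. Here r is also an assumption.

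| c | r | Bias (points) | Rejection rate |
|---|---|---|---|
| 0.9 | 0.3 | 0.59 | 6.1% |
| 0.8 | −0.2 | −0.70 | 6.4% |
| 0.8 | 0 | 0 | 5.0% |
| 0.8 | 0.1 | 0.35 | 5.4% |
| 0.8 | 0.3 | 1.05 | 8.3% |
| 0.8 | 0.5 | 1.76 | 14.2% |
| 0.6 | 0.5 | 3.23 | 31.9% |

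The two models agree. At c = 0.8 and r = 0.3, a bias of 1.05 corresponds to D = 1.05/0.2 = 5.3 points, inside the assumed range. The SD of 10.04 is not reduced for baseline adjustment, so for a given r these bias figures are upper values.

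Neither calculation puts a number on therapist judgement being influenced by improvement. The article offers no basis for one.

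**4. What a complier average effect would target.** With no access to the intervention in care as usual, non-compliance is one-sided, and the estimate is roughly the intention-to-treat effect divided by c. If the intention-to-treat effect is zero, so is the target. Otherwise it is larger by a factor of 1/0.9 = 1.11 to 1/0.7 = 1.43. If non-completers gain something from partial treatment, the estimate is too large by (1 − c)/c times their mean gain, which is one quarter of that gain at c = 0.8.

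**The case against.** The other side has several good points.

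- **Nothing confirmatory rests on this analysis.** The primary and secondary outcomes are analysed by intention to treat, and this is one of four supportive analyses. That stands, and it limits the weight of the point.
- **The direction is not established.** A reader might infer that the analysis must be biased towards CBT. The article gives neither a completion rate nor a link between completion and prognosis, and the working shows zero or reversed bias under equally permissible inputs. Favouring CBT is plausible, no more.
- **The size rests on assumptions.** The 2.4-point figure pairs the worst value of each input, and D must be read as what remains after baseline CIS-fatigue is in the model. A raw difference of 4–8 points would give less. At 80% completion with r between 0.1 and 0.3, false rejection is 5.4–8.3%, which is modest.
- **The whole care-as-usual arm as comparator is an inference.** The text does not say so. But completion as defined cannot apply to that arm, and taken literally the rule would leave no controls, so no other workable reading is offered.
- **Definition (b) is not shown to follow the outcome.** Cases are discussed in bi-weekly supervision, the outcome is self-reported online, T2 comes six months after T1, and nothing shows therapists seeing the scores. The exposure is a possibility created by the missing criterion.
- **Definition (a) is already close to a sound compliance rule, and a complier average test largely repeats the intention-to-treat test.** Both are true. The complier estimate should therefore not be presented as an independent robustness check either.

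The completion criterion and the comparator could be elaborated in an analysis plan that is not shown. The one-sided selection and its label as a robustness check, however, are stated in the article.

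**Conclusion.** The point holds in a limited form. As described, the per-protocol analysis breaks the randomised comparison by selecting on post-randomisation behaviour in one arm. It can show a difference when there is no treatment effect, and it cannot by itself demonstrate that the intention-to-treat result is robust. Definition (b) is the weaker of the two.

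Under assumed completion of 70–90% and an assumed residual prognostic difference of 4–8 points, the bias is about 0.4–2.4 CIS-fatigue points, or 7–40% of the 6-point target. It vanishes if completion is unrelated to prognosis and changes sign if those who recover early stop treatment.

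Two stronger conclusions are not supported. One is that the analysis is worthless: definition (a) uses observable actions, and the effect among completers is a legitimate question when labelled as such. The other is that the trial's main conclusion is in doubt: the primary analysis keeps all randomised participants in their allocated arms and is untouched by this.

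**What to change.** - **Estimate the effect of completing treatment as a complier average causal effect.** Use randomisation as instrument (two-stage least squares or equivalent), with baseline CIS-fatigue and the two stratification factors, acute illness severity and MRC dyspnoea, as covariates.
- **Define compliance by definition (a).** Take it from the platform logs and the therapist-registered modules, which also cover face-to-face delivery. State which modules count as standard, because the Intervention section speaks of core modules.
- **Report it as supplementary.** Describe it as an estimate of a different quantity and not as a robustness check of the intention-to-treat result. State the exclusion restriction, and say that partial exposure among non-completers may strain it.
- **Keep therapist-judged completion as description only.** Label any retained per-protocol comparison as supplementary and non-randomised.

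The cost is a change of wording in the analysis plan before analysis. The data are already being recorded, so nothing new has to be collected. The price is wider intervals and one added assumption.

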### Sample size calculation

The sample size calculation is based on testing the primary hypothesis that CBT leads to a significantly lower mean fatigue severity score (CIS-fatigue) across the first two follow-up assessments (T1 and T2) as compared to care as usual. A difference of 6 points on the CIS-fatigue is considered clinically relevant [38]. Based on previous research we assume a common standard deviation of 12 and correlation coefficients of 0.4 among CIS-fatigue scores assessed at T1 and T2 [27, 31].

With a sample size of 45 in group 1 (CBT) and 45 in group 2 (care as usual), a two-sided test for the time averaged difference between two means in a repeated measures design with a 0.05 significance level has 80% power to detect a difference in means of 6 in a design with 2 repeated measurements when the standard deviation is 12 and the between-level correlation is 0.4. Assuming a conservative dropout of 20%, we will randomise 114 participants, 57 to each condition.

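### Five imputed data sets leave avoidable Monte Carlo error in the p value of the fourth sensitivity analysis; a larger number costs only computing time

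*Protocol article*

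**What the plan says.** The Statistical analyses section of the protocol article tests the primary hypothesis without imputation: "The primary hypothesis will be tested using a mixed linear model". It then adds robustness checks: "To explore the robustness of our findings from the primary analysis, four sensitivity analyses will be conducted". In the fourth of these, "missing values will be replaced with multiple imputation using chained equations and the data will be reanalysed". The number of imputations is stated outright, "A total of five data sets will be imputed and pooled", with pooling by Rubin's rule. The same section applies a two-sided 0.05 significance threshold to every analysis, so this reanalysis will be read against it too.

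The Sample size calculation section gives the planning values: "A difference of 6 points on the CIS-fatigue is considered clinically relevant"; "we assume a common standard deviation of 12 and correlation coefficients of 0.4 among CIS-fatigue scores assessed at T1 and T2"; and "Assuming a conservative dropout of 20%, we will randomise 114 participants, 57 to each condition".

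**The concern.** Multiple imputation draws the missing values at random, so a finite number of data sets leaves simulation noise in the pooled result. At a dropout of 20%, five sets may leave enough noise that the same data, reanalysed with another seed, give a noticeably different p value.

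The only stated purpose of this analysis is to show whether the primary finding is robust. If its p value falls on one side of 0.05 or the other partly by choice of seed, then agreement or disagreement with the primary mixed model may reflect simulation noise and say little about the missing data. The number is a choice the article makes, not a detail it leaves open.

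**Working it through.** **1. The plan's own figure.** Inputs from the Sample size calculation section: difference 6, SD 12, T1-T2 correlation 0.4, two-sided 0.05, 80% power, 20% dropout.

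- SD of the T1/T2 mean: 12 × √((1 + 0.4)/2) = 10.04.
- Required n per arm, normal approximation: 2 × 10.04² × (1.96 + 0.84)² / 6² ≈ 44. With 45 per arm, power is 80.9% (normal) or 80.1% (t test).
- Dropout: 45/0.80 = 56.25, rounded up to 57 per arm, or 114 in total.

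The stated sample size reproduces.

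**2. Seed noise by formula.** With between-imputation variance B and fraction of missing information FMI, the SD of the pooled difference over seeds is √(B/m) ≈ √(FMI/m) × SE. With 57 × 0.8 = 45.6 completers per arm, SE ≈ 10.04 × √(2/45.6) = 2.10. For FMI 0.20:

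| m | √(FMI/m) | SD over seeds (points) | Efficiency 1/(1 + FMI/m) |
|---|---|---|---|
| 5 | 0.200 | 0.42 | 96.2% |
| 20 | 0.100 | 0.21 | 99.0% |
| 50 | 0.063 | 0.13 | 99.6% |

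B is itself estimated on m − 1 degrees of freedom. Its coefficient of variation is about √(2/4) = 71% at m = 5, against √(2/49) = 20% at m = 50. The standard error and the reference degrees of freedom therefore also move with the seed.

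**3. Simulation.** Set-up: 57 per arm, SD 12, T1-T2 correlation 0.4, 20% dropout, Bayesian regression imputation, Rubin pooling with small-sample degrees of freedom, and analysis of covariance on the T1/T2 mean. Assumptions not in the document: baseline to follow-up correlation 0.3, data missing completely at random, three dropout patterns, and 0 or 15 uninformative auxiliary variables. Each scenario used 60 simulated trials, with a true difference of 6 or 4.2 points.

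A run changes side when its p value is on the other side of 0.05 from the many-imputation (limiting) p value. Results at m = 5:

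| Dropout pattern | FMI | SD over seeds (points) | Runs changing side, true difference 6 | Runs changing side, limiting p 0.01 to 0.10 |
|---|---|---|---|---|
| All miss T1 and T2 | 0.20-0.22 | 0.40-0.44 | about 6% | 17-26% |
| Half still give T1 | 0.13-0.14 | 0.30-0.34 | 4% | 16-19% |
| Only T2 lost | 0.08-0.09 | 0.23-0.25 | 0-2% | 2-13% |

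The SD over seeds is 12 to 21% of the simulated standard error. It is 0.23/6 ≈ 4% to 0.44/6 ≈ 7% of the 6-point difference. In the first pattern, raising m to 50 lowers the last column to about 3 to 10%. The last column rests on 8 to 27 simulated trials per scenario and is approximate.

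**4. What this does to one p value.** Four simulated data sets, all dropouts missing both visits; central 95% of p over seeds, with the share of runs above 0.05 in brackets:

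| Limiting p | m = 5 | m = 20 | m = 50 |
|---|---|---|---|
| 0.005 | 0.001-0.038 (1%) | 0.003-0.011 (0%) | 0.003-0.008 (0%) |
| 0.020 | 0.006-0.082 (13%) | 0.010-0.039 (0.4%) | 0.014-0.032 (0%) |
| 0.030 | 0.008-0.113 (30%) | 0.016-0.055 (6%) | 0.020-0.045 (0%) |
| 0.037 | 0.011-0.127 (39%) | 0.021-0.070 (18%) | 0.026-0.055 (9%) |

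**The case against.** A reader might infer that the estimated CBT effect itself would change materially with the seed, or that five imputations make the analysis invalid. The document's figures support neither. In the worst pattern the SD over seeds is at most about 0.44 points, against a standard error of about 2.1 and a relevant difference of 6, and the pooled estimate keeps 96 to 98% efficiency. Rubin's rule adds B/m to the variance and uses a reduced-df reference distribution, so finite m is already allowed for. What it costs is some efficiency and reproducibility.

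Three further objections carry weight:

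- **Amount of missing data.** The article calls 20% conservative. Under Outcome measures, late responders are contacted and reluctant participants are asked to give at least the primary measure. If many dropouts still give T1, the milder rows of the table apply.
- **Dependence on p.** Changes of side are common only when p is already near 0.05. At the planned effect they are about 6% of runs or fewer.
- **Role of the analysis.** It is one of four sensitivity analyses. The primary mixed model uses no imputation, and nothing in the article makes the trial's conclusion depend on this check.

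All three limit the size of the point. None gives a reason for stopping at five. High efficiency describes the precision of the estimate and does not make its p value reproducible.

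**Conclusion.** The point holds as a minor one. At m = 5 the p value of the fourth sensitivity analysis is poorly reproducible: near 0.05, roughly 2 to 26% of seeds land on the other side of the threshold, depending on which visits dropouts miss. The effect estimate is stable enough for any clinical reading, the inference is valid, and the primary estimate and p value are untouched.

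The ranges rest on 20% dropout, data missing completely at random, a baseline to follow-up correlation of about 0.3 and the three dropout patterns shown. Less missing data than this would shrink them. The absence of a seed or a Monte Carlo criterion from the article is not counted against it, since the full plan is not shown.

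**What to change.** In the Statistical analyses section, replace five imputed data sets with a larger number, for example 50, and run the imputation with a recorded seed. Reporting the Monte Carlo error of the pooled difference would let readers judge what noise remains.

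Fifty is a convenient choice, not a derived threshold. Twenty already halves the SD over seeds, since √(5/20) = 0.5, and fifty cuts it to about a third, since √(5/50) = 0.32. Even at 50 a p value very close to 0.05 can still change side, so the pooled difference and its interval should be read alongside it.

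The change alters one number in the plan and costs only computing time. It needs no further data and leaves the primary analysis as it is.
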